## Abstract

**Background:**

Lead has been associated with adverse health effects, especially neurocognitive and behavioural effects, in children. Communities living close to mining land are at risk of elevated exposure to lead.

**Methods:**

This paper outlines a before and after intervention study protocol to evaluate the impact of a personal and domestic hygiene intervention on lead exposure in a community located adjacent to a mine dump. In each participating household, parents or guardians will be interviewed using a structured questionnaire to obtain information on socio-demographic characteristics, living conditions, domestic hygiene practices and potential alternative sources of exposure to lead. A registered nurse will collect hand wipe samples from children aged one to five years, for whom parental consent and where possible child assent has been obtained. Environmental dust samples will be collected from the floors and/or windowsills of children’s dwellings for lead content analysis. Soil samples will be collected from yards to determine lead content. An educational intervention will then be applied to the intervention group, including the engagement of households or guardians in an educational discussion on the sources, pathways of exposure, health effects of lead exposure and protective measures, with the aid of a specially designed educational brochure. Data will be analysed for descriptive and inferential statistics using Stata version 16.

**Discussion:**

The study will determine whether the intervention led to a reduction in indoor dust lead levels, and if shown to be effective, will inform the development of an awareness campaign to reduce lead exposure in communities located in close proximity to mine dumps.

**Trial registration:**

The study is retrospectively registered on ClinicalTrials.gov Protocol Registration and Results System with registration number NCT05265572 and first release date of 18^th^ February 2022.

## Background

Lead is a pervasive environmental toxicant and is associated with a spectrum of adverse health effects [1]. No safe threshold for lead exposure has been identified; however, the Centers for Disease Control and Prevention adopted a reference level of 5.0 μg/dL in 2016 for public health intervention concerning exposure to lead [2]. This level is related to the distribution of population and will be regularly reviewed. Notably, the World Health Organization has listed lead among the top ten toxic metals of public health concern [3]. Exposure to lead has been associated with behavioural disorders, especially in children who are particularly susceptible to its detrimental effects. In some parts of South Africa, residential areas have been developed very close to mine dumps [4] with an estimation of 1.6 million people living in settlements directly next to mine dumps [5, 6]. Mine dumps consist of a complex mixture of dust and particles, to which metals and other harmful substances may be attached. The dumps are major generators of wind-blown dust, which may contain metals such as lead, with potential risk to human health in exposed communities [4, 7, 8], posing a greater risk of elevated blood lead levels in children [9]. Children, especially those under the age of five years, are recognized to be a group that is particularly vulnerable to lead, both in terms of exposure and the health consequences [10]. Such detrimental health effects may include stomach cramps, kidney dysfunction, anaemia, constipation and high blood pressure [10]. Lead may also influence children's physical growth and body composition through several biological mechanisms [11].

## Methods

### Study design and population

A before and after intervention study will be conducted with a control and intervention group. This study follows a descriptive, correlational and experimental design [12]. The study area has a population of 4008 with 1124 households situated in Johannesburg Metropolitan Municipality adjacent to the Durban Roodepoort Deep Mine Dump. Figure 1 shows the intervention and control groups within the study area. The study targets children between the ages of one and five years. Children whose parents have not consented to any part of the research, or children who have not agreed, will be excluded from the study. Only parents/guardians over the age of 18 years will be included in the study.

**Fig. 1 Fig1:**
[figure not shown]
Map of Snake Park showing control and intervention group (source: [name], South African Medical Research Council)

The map of the study area reflecting household street names and stand numbers will be used to stratify single dwellings in close proximity (within 500 m) to the mine dump. Households located in the intervention group will be randomly selected and matched by structure and type (e.g. government-funded houses or non-government funded houses) with a dwelling in the control group.

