### Determination of the sample size

Strata will be defined according to two main divisions within the catchment area. Systematic random samples will be taken within each division where every Xth dwelling will be sampled. Sample sizes were calculated at 80% power. The number of households per group is increased by 5% to account for possible loss to follow-up. To detect a mean difference in change from baseline to follow-up of -3 μg/dL between the control and experimental groups i.e., a lower lead level by 3 μg/dL in the intervention group compared to the control group, with 80% power and common standard deviation of 11 μg/dL, a sample of 213 households per group is required. To account for LTFU the number of households per group is adjusted to 224. Therefore 448 households are to be recruited and randomized to control and experimental groups accordingly.

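### The protocol gives unreconciled rules for how dwellings enter the two groups (matching, every-Xth sampling, randomization), and the role of the 500 m limit is unclear, so balance in distance to the dump is not assured

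*Protocol article*

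**What the plan says.** The protocol article describes selection and allocation in several places.

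- **Study design and population:** "Figure 1 shows the intervention and control groups within the study area". The figure is a map of the settlement.
- **Text under Fig. 1:** the map is used to "stratify single dwellings in close proximity (within 500 m) to the mine dump". Then: "Households located in the intervention group will be randomly selected and matched by structure and type", the match being with a control dwelling. Structure and type are the only matching factors given.
- **Determination of the sample size:** the strata here are two divisions of the catchment area, with no distance given. The draw is then described: "Systematic random samples will be taken within each division where every Xth dwelling will be sampled". The section ends: "Therefore 448 households are to be recruited and randomized to control and experimental groups accordingly".
- **Data collection procedure:** participants are allocated to a group in phase one, with a pointer to Fig. 1.
- **Data analysis plan:** change from baseline is modelled with a group effect and covariates. The adjustments named are lead levels in homes and important baseline characteristics, including questionnaire variables. Distance to the dump is not named.

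**The concern.** The Background identifies wind-blown dust from the dump as the exposure of interest, so closeness to the dump is an obvious determinant of how fast a cleaned surface collects lead again. The rule that forms the groups decides whether they are comparable on it.

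The text offers three rules. Each implies a different kind of control group: chosen by resemblance to a partner, chosen by position in a list, or formed by chance from one recruited pool. Only the last gives a randomized comparison. The strata are also worded in two ways, and 500 m could be an eligibility limit for everyone, a stratum boundary, or a limit on one group.

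At stake is whether a difference in change between groups can be attributed to the hygiene intervention, and whether the trial may be reported as randomized.

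**Working it through.** **1. The plan's own figure.** Inputs from the sample size section: difference 3 μg/dL, SD 11 μg/dL, power 80%. The Data analysis plan gives the 5% level; two-sided is assumed.

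- Normal approximation: n = 2 × (1.960 + 0.842)² × 11² / 3² ≈ 211.1, so 212 per group.
- The t-test version gives 212.01, rounded up to 213, as stated.
- 213 × 1.05 = 223.65, so 224 per group and 448 in total.

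The sample size reproduces. The point does not touch it.

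**2. Can the rules be combined?**

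- *Frame plus strata.* Single dwellings within 500 m could be the frame and the two divisions the strata, with every Xth dwelling drawn. This reconciles the two wordings of the strata. It does not produce matched controls: a dwelling that enters by list position does not enter because it resembles a partner.
- *Systematic draw for intervention households, matching for controls.* Random selection of intervention households fits both sections. But the every-Xth rule is stated for each division, not for one group, and nothing is left to randomize.
- *Recruit 448, then randomize.* Matching then has no stated role. The text under Fig. 1 also speaks of households located in the intervention group being selected, which puts group membership before selection. Randomization after recruitment reverses that order.

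Each reading leaves at least one sentence unmet. X also depends on the frame: with all 1124 households it is 1124 / 448 ≈ 2.5, and with a 500 m limit it would be smaller if that limit excludes any households.

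**3. What balances distance under each rule?**

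| Rule followed | Balance in distance to the dump |
|---|---|
| Randomization of the 448 | In expectation |
| Matching on structure and type, groups as areas | None beyond the 500 m limit, if it binds both groups |
| Every Xth dwelling, groups equal to divisions | None beyond the 500 m limit, if it binds both groups |

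**4. Sensitivity, on assumed values.** The documents give no distance effect, so this is not a prediction. Take 213 per group and SD 11, so SE = 11 × √(2/213) = 1.066. Let b be a spurious difference in change due to distance.

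- Error rate with no true effect = 1 − Φ(1.96 − b/SE) + Φ(−1.96 − b/SE).
- Power against a true difference of 3 when b acts against the intervention = Φ((3 − b)/SE − 1.96).

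| b (μg/dL) | Two-sided error | Power |
|---|---|---|
| 0 | 5.0% | 80% |
| 0.5 | 7.6% | 65% |
| 1 | 15.5% | 47% |
| 1.5 | 29.1% | 29% |
| 2 | 46.7% | 15% |

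**The case against.** Three stronger readings are tempting, and the documents do not support them.

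- **That distance plays no part in the strata.** The sentence under Fig. 1 ties 500 m to stratifying. What is unclear is its role and whether it binds both groups.
- **That dwellings beyond 500 m are admitted.** The sample size section merely does not repeat the limit, and silence is not permission. If 500 m is the frame for both groups, the possible difference in distance is bounded, although the groups can still differ within 0 to 500 m. Fig. 1 may show the distances. It was not available for this review, and nothing is held against the plan on that account.
- **That the groups do differ in distance and the result is biased.** If the 448 households are truly randomized, distance is balanced in expectation and the bias argument falls. That the two divisions are the two groups is also only an inference.

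The analysis offers further protection. Change from baseline is modelled, and the hand-wipe model adjusts for lead levels in homes, which deals with much of a difference in starting level. The open wording on baseline characteristics could accommodate distance.

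All of this stands and limits the point. It does not remove the conflict among matching, every-Xth sampling and randomization, which is in the printed text and not a detail left to a fuller document. Nor does adjustment for home lead levels ensure removal of a distance-related difference in the rate of re-accumulation over the three months, and change over that period is what the groups are compared on.

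**Conclusion.** The selection and allocation rules contradict one another and need reconciling, including the statement that households are randomized. This rests on the text alone and requires no assumption about Fig. 1.

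The consequence for bias is conditional. If the groups are map areas, the matching factors and the named adjustments do not balance closeness to the dump, and a distance-related difference in change could imitate or mask an effect. Its size cannot be stated from the documents. The sensitivity table shows only that, against a target of 3 μg/dL, an assumed difference of 1 μg/dL would matter. It assumes 213 analysed per group, SD 11, a two-sided 5% test and no adjustment for distance. If allocation was truly randomized, what remains is a reporting contradiction.

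**What to change.** 1. State the one selection and allocation rule actually used, in the same terms under Fig. 1 and in the sample size section. Remove or reconcile the others, including the sentence on randomization.
2. State that the same distance limit applies to both groups or, if it does not, report the range of distances in each.
3. Compute each household's distance to the dump from the existing stand map. Include it, with dwelling structure and type, as a covariate in the change models.
4. If allocation was by area, describe the comparison as non-randomized.

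**Cost.** A wording amendment, desk work on a map the team already plans to use, and two named covariates. The Study progress section says data collection has begun, so re-selecting households is not proposed; distance can still be computed for those already visited. The downside is some loss of precision if distance and group are strongly correlated. In that case the data hold little information for separating the two, and the report should say so.

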### Determination of the sample size

Strata will be defined according to two main divisions within the catchment area. Systematic random samples will be taken within each division where every Xth dwelling will be sampled. Sample sizes were calculated at 80% power. The number of households per group is increased by 5% to account for possible loss to follow-up. To detect a mean difference in change from baseline to follow-up of -3 μg/dL between the control and experimental groups i.e., a lower lead level by 3 μg/dL in the intervention group compared to the control group, with 80% power and common standard deviation of 11 μg/dL, a sample of 213 households per group is required. To account for LTFU the number of households per group is adjusted to 224. Therefore 448 households are to be recruited and randomized to control and experimental groups accordingly.

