### Data collection procedure

Data will be collected using multiple methods, namely, 1) a structured questionnaire; 2) hand dust wipe samples from children aged between one and five years; 3) floor and/or windowsill dust wipe samples; and 4) yard soil samples. These methods will be applied in two phases. In phase one, participants will be allocated into either the control or intervention group (see Fig. 1). Both the control and intervention groups will be interviewed, household floor and/or windowsill dust wipes will be taken, yard soil samples collected, and hand dust wipe samples taken from children in participating households. The intervention group will participate in the domestic hygiene demonstration and educational discussion. The intervention group will be allowed a period of three months to apply the domestic hygiene intervention. Each household will be given a diary to record their daily cleaning patterns. During the three months, a monthly reinforcement visit will be undertaken to follow-up and encourage the sustained application of the intervention. In phase two, after three months, both the intervention and control group will be visited to collect a repeat floor and/or windowsill dust sample, yard soil sample and hand dust wipe sample from children. Feedback will be obtained from the intervention group on the experience of the intervention using a checklist.

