### The intervention

#### Personal hygiene intervention

At the end of the questionnaire-based interview, blood collection and environmental sample collection, participants (parents/guardians) will be engaged in an educational discussion for approximately 30 min, with the aid of a specially designed educational pamphlet (Fig. 2). The pamphlet contains information about health effects potentially associated with dust exposure from mine dumps and the personal hygiene and domestic hygiene steps that may be followed to reduce dust exposure. The pamphlet will be pre-tested during the pilot study and refined as necessary.

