### Data analysis plan

Descriptive statistics such as means, medians, standard deviations, interquartile and 95% confidence intervals will be used to describe lead levels and other continuous outcomes. Frequencies and proportions with 95% confidence intervals will be calculated for categorical variables. The paired t-test will be used to compare the difference in lead levels within groups between baseline and follow-up. The two-sample t-test will be used to compare the mean lead levels between groups. McNemar’s test will be used to compare the children’s health outcomes between baseline and follow-up. The change from baseline to follow-up will be modelled, with a group main effect, with adjustment for other covariates. A linear mixed-effects model will be used to model the change in lead levels resulting from the hand dust wipes, with the main effect for the group. Adjustments will be made for lead levels in homes, as well as other important baseline characteristics, including variables from the administered questionnaire. The model will be adjusted for clustering within the household. Depending on the level of missingness, imputation of follow-up data may be conducted, and analysis rerun as sensitivity analysis. Statistical significance is taken at a 5% level. All analyses will be conducted using STATA 16.

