## Discussion

A research study has shown that there has been significant growth in the number of households and housing developments, close to the TSFs in South Africa [15]. Furthermore, the study stated that the implications for many residences downwind mine dumps justify ongoing monitoring efforts and educational programmes [14]. Occasionally, two strategies are implemented to reduce pollution from such mine dumps i.e., spraying of mine tailings dumps with water and rehabilitation through planting grass. However, these strategies are often deemed ineffective, since grass withers during the dry season in particular, and sprayed water is rapidly absorbed or evaporated. The current extent of environmental contamination from mine dumps and potential health impacts in nearby areas has been researched, the findings showed that participants identified mine dumps as the biggest source of dust [16]. Other studies have explored the acceptability and feasibility of changing housekeeping behaviour to reduce childhood lead exposure [17]. A study by Feit et al. found that certain personal and domestic hygiene interventions were feasible and acceptable to the study community and were significantly associated with a reduction in indoor dust lead concentrations [16]. However, there is a need to conduct further trials in developing countries to determine the effectiveness of interventions for the prevention of lead [18]. A review by Nussbaumer-Streit et al. found that educational interventions were not effective in reducing blood lead levels and dust control interventions may lead to little or no difference in blood lead levels [19]. However, the quality of evidence was moderate to low, meaning that future research is likely to change these results. No further research has yet been undertaken to evaluate the impact on childhood lead levels of a community-based lead exposure reduction programme focused on personal and domestic hygiene. In particular, there remains a gap in knowledge regarding household hygiene interventions to reduce exposure to lead in communities living close to mine dumps in South Africa, particularly among children. This study, which intends to evaluate the impact of a household hygiene intervention comprised of an educational and domestic household hygiene intervention to reduce mining-related dust exposure, will address this need. The study holds the potential for a cost-effective measure to reduce exposure to mining-associated toxic substances, for hundreds of thousands of households living in the shadow of mining operations and other sites of elevated exposure to toxic substances from industrial sources.

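### The sample size is justified in μg/dL, a unit that fits none of the outcomes the protocol describes, so the 80% power holds only for a standardised difference of about 0.27 SD

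*Protocol article*

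**What the plan says.** The Protocol article, under Determination of the sample size, states the target as "To detect a mean difference in change from baseline to follow-up of -3 μg/dL between the control and experimental groups". It continues: "with 80% power and common standard deviation of 11 μg/dL, a sample of 213 households per group is required". The number is raised by 5% for loss to follow-up, to 224 per group, and the section ends: "Therefore 448 households are to be recruited and randomized to control and experimental groups accordingly". It speaks of a lead level without naming the sample that would be assayed.

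The Data collection procedure lists four sources. It begins "Data will be collected using multiple methods, namely, 1) a structured questionnaire; 2) hand dust wipe samples from children" and goes on to floor or windowsill dust wipes and yard soil. The three-month visit repeats dust, soil and hand wipes. The laboratory sections cover those three sample types and no others, and floor and windowsill dust is compared with standards in µg/ft².

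The Data analysis plan refers to lead levels in general for the t-tests and for one change model, and specifies a mixed model for hand-wipe lead. The Discussion paragraph of the Abstract says the study will answer the question for indoor dust lead.

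Blood sampling appears once, under Personal hygiene intervention, where the educational discussion is placed as follows: "At the end of the questionnaire-based interview, blood collection and environmental sample collection".

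**The concern.** A sample size calculation tells the reader which effect, on which outcome, the trial can detect. Here the difference and the SD are in a unit that none of the three listed sample types is reported in. Wipe lead is a mass per area or per wipe, and soil lead is a content of solid material. The figures of 3 and 11 cannot be converted to either.

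This affects how the result can be read. If the comparison of hand-wipe or dust lead is not significant, the protocol gives no basis for calling it adequately powered, because the smallest detectable difference on that scale is unknown. The fault lies in what the document states: the stated calculation does not match the stated outcomes. It is not a detail that a condensed article could leave to a fuller document.

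**Working it through.** **Inputs.** Difference in change 3 and SD 11 (both μg/dL), 80% power, 1:1 allocation and a 5% addition for loss, all from Determination of the sample size. The 5% significance level is from the Data analysis plan ("Statistical significance is taken at a 5% level"). Sidedness is not stated; two-sided is assumed and checked in step 1.

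**Step 1: reproduce the plan's figure.**
- Standardised difference: 3/11 = 0.273.
- Normal approximation: n per group = 2 × (1.96 + 0.8416)² × (11/3)² = 211.05, rounded up to 212.
- With the t distribution: 212.01, rounded up to 213, which is the protocol's figure.
- Power at 213 per group: 80.4% (normal) or 80.2% (t).
- A one-sided 5% test would need 167 per group, so the two-sided reading is the one that fits.
- Loss allowance: 213 × 1.05 = 223.65, rounded up to 224; 2 × 224 = 448. Both match.

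The μg/dL inputs therefore did produce the stated number, and the arithmetic is sound.

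**Step 2: compare the unit with each described outcome.**

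| Outcome | Collected at both visits | Assay described | Could be in μg/dL |
|---|---|---|---|
| Child hand-wipe lead | yes | yes | no |
| Floor or windowsill dust lead | yes | yes (judged in µg/ft²) | no |
| Yard soil lead | yes | yes | no |
| Blood lead | not listed at either visit; one passing mention | none | yes |

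The only quantity that the unit would suit has no sampling procedure, assay, follow-up sample or analysis. Even if blood were drawn at baseline, the listed follow-up would not give the change on which the calculation is based.

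**Step 3: what carries over.** Only the ratio 3/11 has no unit. With 213 analysed households per group, a two-sided 5% test has about 80% power for 0.273 × s, where s is the SD of change in the measured outcome. The document gives no s for hand-wipe, dust or soil lead, so this cannot be put in absolute terms.

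**Step 4: sensitivity.** The standardised effects below are assumptions, because the documents give none for a measured outcome (normal approximation, two-sided 5%).

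| Assumed effect (SD of change) | Power at 213 per group | Households per group for 80% |
|---|---|---|
| 0.10 | 18% | 1570 |
| 0.15 | 34% | 698 |
| 0.20 | 54% | 393 |
| 0.25 | 73% | 252 |
| 0.273 | 80% | 212 |
| 0.30 | 87% | 175 |
| 0.40 | 98% | 99 |

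**The case against.** The best defence is that the number keeps a meaning. In standardised terms, 213 per group gives 80% power for 0.27 SD of change in any continuous household outcome, and the t-tests and general change model refer to lead levels without restriction. That stands. It would be wrong to infer that the calculation says nothing about the described outcomes; what is missing is the step to an absolute difference in a measured unit.

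A second defence is that μg/dL is a slip for another unit. The documents do not exclude this. But the intended unit and outcome would still have to be stated, since a reader cannot tell whether 3 and 11 refer to hand, floor, windowsill or soil lead.

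Some stronger readings are tempting and are not supported:
- A reader might infer that the trial takes no blood at all. The Personal hygiene intervention section mentions blood sampling, so the supported statement is that no blood-lead procedure, assay, follow-up sample or analysis is described and that the passages conflict.
- A reader might infer that the target is explicitly a blood-lead difference. The sample size section does not say blood, and the Background sentence giving the 5.0 μg/dL reference level speaks of lead exposure without naming blood. The blood reading rests on the unit alone, and the point does not depend on it.
- A reader might use the cited review, by which "dust control interventions may lead to little or no difference in blood lead levels", to argue that a 3 μg/dL effect is implausible. The next sentence of the Discussion rates that evidence as moderate to low and likely to be changed by further research. A target difference also need not be an expected effect. This argument is not relied on here.

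**Conclusion.** The point holds as a mismatch between the unit of the sample size calculation and the outcomes described. It is not an arithmetic error. The 213 (224) households per group and the 80% power are stated for a difference of 3 μg/dL with SD 11 μg/dL, and no described outcome is measured in that unit. What the calculation supports is about 80% power for 0.27 SD of change, assuming a two-sided 5% test, one value per household and 213 analysed per group. Whether 0.27 SD is a realistic or worthwhile effect on hand-wipe or dust lead cannot be judged from the document. Across assumed effects of 0.10 to 0.40 SD, power ranges from 18% to 98%. It does not follow that the trial is underpowered; its power for its own outcomes is simply not established.

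**What to change.** 1. Name the outcome that sizes the trial. The document points two ways: the Abstract to indoor dust lead, and the mixed model in the Data analysis plan to hand-wipe lead. The sponsor must choose and say so.
2. Restate the target or detectable difference, and the power at 213 analysed households per group, in that outcome's unit and on the scale on which it will be analysed.
3. Take the SD of change from the pilot or from early data, if either provides it. The article says only that the pilot is complete, not that it measured any outcome twice. Early data should be used pooled, without comparing the groups. If no SD is available, show the detectable difference as 0.273 × s over a stated range of s.
4. Reconcile Determination of the sample size, Data collection procedure and Personal hygiene intervention on whether blood is collected. If it is, state at which visits and how it is assayed and analysed. If it is not, remove the mention.

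Data collection has begun, so this should be settled before outcomes are compared between groups. The cost is one recalculation and a wording amendment. Correcting the statement needs no extra households. The downside is that the restated power may be less favourable than 80%.

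### The protocol both randomises households and treats the two groups as places on a map; the allocation used must be stated, because if the arms are areas the area and the intervention cannot be separated

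*Protocol article*

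**What the plan says.** The protocol article describes how households reach a group in three places.

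- **Determination of the sample size:** "Therefore 448 households are to be recruited and randomized to control and experimental groups accordingly". The same section says "Strata will be defined according to two main divisions within the catchment area" and "Systematic random samples will be taken within each division where every Xth dwelling will be sampled".
- **Study design and population, including Fig. 1 and the text below it:** "Figure 1 shows the intervention and control groups within the study area". The caption reads "Map of Snake Park showing control and intervention group", and the text under it says "Households located in the intervention group will be randomly selected and matched by structure and type", the match being a dwelling in the control group.
- **Data collection procedure:** in phase one, "participants will be allocated into either the control or intervention group (see Fig. 1").

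The Data analysis plan compares the groups with two-sample t-tests and with models of change from baseline. For the hand-wipe mixed model it says "The model will be adjusted for clustering within the household". It names no area term.

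**The concern.** If households are recruited first and then randomised, no household can be in the intervention group before it is selected. Yet the text below Fig. 1 starts from households that are already there. The only random step described in any detail is the sampling of dwellings. That makes the sample representative of its area, but it does not make the two groups comparable.

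What the main comparison can mean depends on the answer. If the arms are areas, the comparison is between two places. The Background calls mine dumps major generators of wind-blown dust. Wind, season or activity at the dump could change lead differently in the two places over three months. Change scores and baseline covariates remove stable differences in level, but they do not remove differences in change. The planned standard errors would also be too small, because they treat households in one area as independent.

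**Working it through.** **1. The statements side by side**

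| Section | When the group is fixed | What is random |
|---|---|---|
| Determination of the sample size | after recruitment | allocation of households, and also sampling of dwellings within two divisions |
| Study design and population, with Fig. 1 | before selection, by location | selection of households within the intervention group |
| Data collection procedure | at phase one, by reference to Fig. 1 | not stated |

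The first two rows cannot both describe one trial. This conflict is in the text and does not need the missing figure.

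**2. The plan's own figure**

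Inputs from Determination of the sample size: difference in change 3 μg/dL, SD 11 μg/dL, power 80%, 5% added for loss to follow-up. The 5% significance level is from the Data analysis plan. Its sidedness is not stated, so two-sided is taken.

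- Normal formula: n = 2 × (1.96 + 0.84)² × 11² / 3², which rounds up to 212 per group. The t-based solution is 212.01, rounded up to 213. A one-sided test would give 167, which does not fit.
- Loss to follow-up: 213 × 1.05 = 223.65, rounded up to 224. Total 2 × 224 = 448.

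So 213, 224 and 448 reproduce, with households independent and no area component. That is right for individually randomised households.

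**3. If each arm is one area (conditional)**

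Assumption: area-level ICC ρ of the change in lead. The documents give no value, so a range is shown.

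- Design effect: DE = 1 + (213 − 1) × ρ
- Effective households per arm: 213 / DE
- True type I error of the nominal 5% test: 2 × [1 − Φ(1.96 / √DE)]

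| ρ (assumed) | DE | Effective n per arm | True type I error |
|---|---|---|---|
| 0 | 1.00 | 213 | 5% |
| 0.001 | 1.21 | 176 | 7.5% |
| 0.005 | 2.06 | 103 | 17% |
| 0.01 | 3.12 | 68 | 27% |
| 0.02 | 5.24 | 41 | 39% |

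With one area per arm, the degrees of freedom for between-area variance are 2 × (1 − 1) = 0. The trial's own data could not estimate ρ, and more households per area would not help.

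**4. The same point without an ICC**

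The household-level standard error is 11 × √(2/213) = 1.07 μg/dL. Suppose the areas differ in three-month change by d for reasons unrelated to the intervention. The chance of a significant result is Φ(d/SE − 1.96) + Φ(−d/SE − 1.96). This gives 15.5% for d = 1, 47% for d = 2 and 80% for d = 3 μg/dL.

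**The case against.** The strongest reply is that one area per arm is not stated anywhere. The map is not shown, and a map of individually marked dwellings could carry the same caption. The two divisions are called strata, and no sentence equates a division with an arm. The phase-one wording describes an act of allocation and is compatible with randomisation. This stands: a reader might infer that the protocol establishes one area per arm, but the documents do not go that far. It does not remove the conflict with the text below Fig. 1.

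A reader might also take 17% to 39% as this trial's error rate. The documents do not support that. The ICC is assumed, it applies to change rather than level, and dwellings within 500 m of the same dump may differ little in change. Values at or near zero are possible.

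The plan also has safeguards. Dwellings are matched on structure and type, and the hand-wipe model adjusts for home lead and other baseline characteristics. These reduce confounding, but they do not address differences in change between areas or supply an area-level standard error.

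Finally, the claim of randomisation is confined to one sentence on sample size. The Abstract and the design statement call this a before-and-after study with a control group. It would be unfair to say that the article presents itself throughout as a randomised trial. The one sentence still determines how the result would be read.

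**Conclusion.** The contradiction is certain and must be resolved: the sample size section cannot be reconciled with the design section as written, and the data collection section points to the map.

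The consequence is conditional. If allocation was by area, the group effect is confounded with any area difference in three-month change, and the planned tests understate the uncertainty. The tabulated figures illustrate how sensitive the error rate is to a small ICC; they do not estimate it for this trial. If households were individually randomised, there is no area inflation, the planned size stands, and the error lies in the design wording and the reference to the map.

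**What to change.** Study progress says that data collection has commenced, so the first step is to establish and report the allocation actually used. Then make Study design and population (with Fig. 1), Determination of the sample size and Data collection procedure agree.

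- **If households were randomised:** state the unit and the procedure, remove the wording that places households in the intervention group before selection, and reflect any matching in the analysis. The two-sample t-test ignores pairs.
- **If allocation was by area:** delete the claim of randomisation and describe a non-randomised controlled before-after comparison. Adjust for baseline lead, dwelling type and baseline yard-soil lead, and for distance to the dump if it can be derived from the map, since it is not listed as recorded. State that household-level standard errors do not include area-level uncertainty; covariates do not repair this. Limit the causal conclusion promised in the Discussion part of the Abstract and in Possible outcomes.

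The change in yard-soil lead is at most supportive as a check on area drift. Soil is sampled to a depth of up to 10 cm, which may dilute a three-month change in surface dust, so a null difference there could falsely reassure.

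The cost is wording, plus covariates that are mostly planned already. The downside of the area branch is a weaker, but correct, causal claim.
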